### Adverse Events and Dropouts

Adverse events that the study participants reported spontaneously were recorded. The type of harm and its onset time, intensity, and frequency were recorded, and the possible causal relationship with the intervention was assessed. The date, informant, and reason for dropout were recorded for the study participants who discontinued the study. In addition, we assessed whether the interruption was because of an adverse event, the participant’s state of health, personal will, or whether the participant was not reached.

### Blinding (Masking)

Participants and trial personnel were not blinded after the point of assignment to interventions following baseline measurements because of the nature of the interventions and outcomes assessed. Participants knew which group they belonged to because the group-specific exercise routines were followed immediately after randomization, and gaming equipment was provided to those randomized to the intervention group. Trial personnel, in turn, were able to deduce the group from the questionnaires related to the game experience gathered during 2- and 4-month visits from participants randomized to the exergame group.

### Promotion of Participant Retention

Participant retention was promoted with phone contact before the 2-, 4-, and 12-month measurements to ensure participation. Data collection was supported by mailing questionnaires to participants when they did not come to the exercise laboratory for 2-, 4-, and 12-month measurements owing to personal reasons or pandemic constraints. The outcomes collected by mail were OKS, VAS, WHODAS 2.0, KOOS, satisfaction with the operated knee, GUESS, and P-SUS scores.

### Data Management

The management of the collected and generated data was documented in the Data Management Plan (DMP) document. The data were pseudonymized and stored securely in locked cupboards or protected network drives. Unidentifiable data were shared with the investigators involved in the study. Processes to promote data quality include the documented data collection protocol and training of data handlers. All research results will be made public through conference presentations or journal publications. Individual study participants will not be identifiable based on public research results. A data monitoring committee was not needed because of the short duration of the trial and the known minimal risks.

### Sample Size

The intended sample size (n=100) of the BEE-RCT was based on the primary outcome, the OKS [22]. Assuming a mean difference of 5 (SD 8) points [40] in a change in the OKS between the groups at 6 to 12 months [40,41], a sample size of 42 in the intervention and control groups was required to detect differences between groups at an α of .05 and reach power of 80%. The dropout rate was estimated to be 10%; consequently, a minimum of 100 participants were needed to be recruited. In 2020, the COVID-19 pandemic decreased the number of elective surgeries, such as TKR, and there were lockdowns in exercise laboratories. Due to this, recruitment slowed in the spring of 2020 and was completely stopped for 3 months because of lockdowns. Consequently, the trial failed to recruit the intended sample size of participants.

### Data Analysis Plan

Repeated measures of the changes in primary and secondary outcomes will be compared between the exergame and standard home exercise groups using intention-to-treat analysis, mixed effects models, and an unstructured covariance structure. Fixed effects included group, time, and group × time interactions. In the primary analysis, repeated measurements will be taken at different time points, including at baseline and at 2 and 4 months. Mixed models allow for the analysis of unbalanced data sets without imputation; therefore, all available data with the full analysis set will be analyzed. In response to the impact of COVID-19, the number of participants is expected to be insufficient for per-protocol analysis. The maintenance of intervention benefits for 12 months will be analyzed using similar mixed effects models as secondary analyses.

A concurrent embedded design of a mixed methods study was used by including a qualitative component within a quantitative study of exercise effectiveness. In the mixed methods approach, quantitative data analysis is mainly descriptive to support the interpretation of qualitative findings. For physical function measures, categorization based on a clinically meaningful level or change from baseline will be used to further integrate the qualitative data. With the qualitative interview data, primarily thematic coding and clustering of the concepts arising from ladder chains are planned [37]. The ladder data will be coded and categorized by 2 researchers and checked until a complete consensus is achieved between them. Integration of quantitative and qualitative data will focus on developing a framework using the identified clusters and structuring them by adopting the interpretative structure modeling technique [42].

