### Random Allocation

After the preoperative baseline measurements, the study participants were randomly allocated one by one to the exergame and standard home exercise groups. A person unrelated to the study had previously used a computer-generated randomization procedure using blocks of 2 and 4 in random order and according to the place of recruitment (Jyväskylä or Turku), gender and baseline Timed Up and Go (TUG) test with time ≤10 seconds (indicating faster performance in patients who had undergone TKR [18,19]). A person unrelated to the study had concealed group allocation cards in opaque sealed envelopes into 4 separate sets of stratification (slow men, slow women, fast men, and fast women) per place of recruitment. After the baseline measurement of each participant, the research physiotherapist of the exercise laboratory opened the next envelope from the appropriate set of envelopes, complying with the allocation stratification, and assigned the participant to the exergame or standard home exercise group according to the group allocation card in the envelope.

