Muscle strength was assessed with isometric knee extension and flexion forces collected using a Metitur Good Strength dynamometer in Jyväskylä (Newton [N]) and a Con-Trex Multijoint dynamometer (Newton-meter [Nm]) in Turku. Knee extension and flexion forces were measured from each lower limb in the sitting position, with the knee angle at 60° of flexion. The measurement sequence was as follows: (1) knee extension, (2) knee flexion force from the nonoperated lower limb, (3) knee extension, and (4) knee flexion force from the operated lower limb. The participants performed 4 warm-up and training contractions with moderate force, after which 4 contractions with maximal force were measured. Thereafter, the performances were repeated until the force improved to <50 N during the knee extension contraction and <20 N during the knee flexion contraction. One contraction lasted approximately 3 seconds, and there was a 30-second break between contractions. All maximal force results were recorded. In addition, after completion of the sets of contractions of the lower limb (eg, knee extensions and flexions of the operated lower limb), the participants were asked if the pain impaired their performance. The direction of painful performance (ie, extension, flexion, or both) and pain intensity on a scale of 1 to 10 were recorded. The best results for knee extension and flexion forces (Nm or N) were used. For analysis, N values were calculated as Nm with the formula Force (N) × lever arm length of the leg (m) and normalized based on body weight (Nm/weight). A higher value in the isometric knee extension and flexion tests indicated better muscle strength.

The range of knee joint flexion and extension was measured using a universal goniometer [27,28]. Measurements were performed on the operated knee in the supine position. First, active and passive knee flexion were measured, followed by active and passive knee extensions. The results were recorded in degrees; a smaller result in extension and larger result in flexion indicated a better joint range of motion.

Knee pain was assessed using the pen and paper version of the VAS [29] by asking participants to rate the average knee pain over a week. The VAS ranges from 0 to 100, indicating no knee pain and the worst possible knee pain, respectively.

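### The stated mixed model leaves out the stratification factors (site, gender, baseline TUG); where these predict change, the group × time test is conservative and loses power

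*Protocol article*

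**What the plan says.** **Design.** Under Random Allocation, the Protocol article stratifies the sequence "according to the place of recruitment (Jyväskylä or Turku), gender and baseline Timed Up and Go (TUG) test with time ≤10 seconds". Block sizes are given separately: "blocks of 2 and 4 in random order". The envelopes were held in "4 separate sets of stratification (slow men, slow women, fast men, and fast women) per place of recruitment", so there are 2 × 4 = 8 strata.

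**Model.** The Data Analysis Plan names the method ("mixed effects models, and an unstructured covariance structure"), the terms ("Fixed effects included group, time, and group × time interactions") and the time points of the primary analysis ("repeated measurements will be taken at different time points, including at baseline and at 2 and 4 months"). Baseline is therefore one of the responses. No site, gender or TUG-stratum term appears. The same type of model is used for the secondary outcomes and for 12 months.

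**Strength.** Under Secondary Outcomes, isometric knee forces were "collected using a Metitur Good Strength dynamometer in Jyväskylä (Newton [N]) and a Con-Trex Multijoint dynamometer (Newton-meter [Nm]) in Turku". For analysis, newton values are converted to newton-metres with the lever arm, and the result is divided by body weight.

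**The concern.** Stratified randomisation balances the arms on the chosen factors. The true sampling variance of the treatment contrast then no longer contains the variation between strata. A model without the strata still counts that variation as error, so its standard error overstates the real uncertainty: intervals are too wide, p-values too large, and the precision that the design secured is not used.

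This matters more here because recruitment stopped at 52 of an intended 100, with 46 having any postoperative measurement (Results). The article itself expects to be underpowered (Strengths and Limitations). The model can still be changed; the recruitment cannot.

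**Working it through.** **1. The plan's own figure.** Sample Size: "Assuming a mean difference of 5 (SD 8) points", α .05, power 80%, 42 per arm. Normal formula, two-sided: n = 2(1.960 + 0.842)² × 8²/5² = 40.2, rounded up to 41. The noncentral t gives 42 per arm with power 80.8%. The figure reproduces, as an unadjusted comparison of change.

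**2. What matters is change, not level.** With baseline as a response, complete data and the stated terms, the 4-month group × time contrast is the difference between arms in 4-month minus baseline. A stratum effect that is the same at every visit cancels from it. Check with 46 participants and an assumed covariance with variances 60 (baseline) and 75 (4 months) and covariance 25: variance of change = 60 + 75 − 2 × 25 = 85, and SE = √(85 × 4/46) = 2.7187. Adding site, gender and TUG stratum as main effects only leaves the SE at 2.7187. A second check with other assumed values gave 2.380 without and 2.380 with main effects, and 2.496 versus 2.497 with 12% of visits missing.

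A simulation agrees (48 participants, 8 strata of 6). When strata explain 10/20/30% of the variance of *level*, the unadjusted type I error is 4.6/4.9/4.5%, close to nominal. When they explain the same shares of the variance of *change*, it is 3.8/2.6/1.8%.

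**3. Power by share of change variance explained (R²).** R² is not in the article; 0 to 0.30 is assumed. Difference 5, SD 8, 23 per arm (46 analysed, equal split assumed). Adjusted SE = 8√(1 − R²) × √(2/23). Power comes from the noncentral t with noncentrality 5/SE; df = 44 unadjusted, 41 with three factors.

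| R² | SE | Power | Gain over unadjusted |
|---|---|---|---|
| not adjusted | 2.359 | 54.5% | – |
| 0 | 2.359 | 54.4% | about 0 |
| 0.05 | 2.299 | 56.5% | 2 points |
| 0.10 | 2.238 | 58.8% | 4 points |
| 0.20 | 2.110 | 63.8% | 9 points |
| 0.30 | 1.974 | 69.6% | 15 points |

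At the planned 42 per arm, 80.8% would become 80.8, 82.7, 84.7, 88.6 and 92.2%.

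**4. Simulation of the allocation.** 46 participants, blocks of 2 and 4 in 8 strata, three independent half-and-half factors with equal effects on change, 6000 runs.

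| R² | Mean model SE, unadjusted | True SE (two runs) | Type I error, unadjusted | Power unadjusted / adjusted |
|---|---|---|---|---|
| 0 | 2.35 | 2.35 | 5.3% | 54.9 / 54.5% |
| 0.10 | 2.35 | 2.22–2.28 | 4.3% | 53.8 / 57.8% |
| 0.30 | 2.36 | 2.02–2.06 | 2.2% | 55.9 / 69.2% |

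A separate simulation with 48 participants and R² 0/10/20/30% gave power 58/57/56/56% unadjusted and 58/62/65/72% adjusted.

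**5. TUG.** Here the stratum is a dichotomised baseline of the outcome. With equal variances and baseline-to-4-month correlation ρ, baseline explains (1 − ρ)/2 of the variance of change, and a median split keeps about 64% of that. ρ, equal variances and the median split are assumptions. For ρ = 0.7/0.5/0.3, R² is about 10/16/22%. Simulated with 46 participants, a standardised effect of 5/8 and only this stratum prognostic, the unadjusted type I error is 4.2/3.3/3.2%, and power rises from 55/53/56% to 59/60/65%.

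**The case against.** **The article is condensed.** The Data Analysis Plan section is short, does not say that these are the only terms, and the full protocol and any SAP are not shown. Covariates are often listed there. This does not remove the point: the article specifies the model down to fixed effects, covariance structure and time points, and that model does not match the allocation described in the same article. If an SAP does include the factors, this section misreports the model and needs correcting anyway.

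**The loss is not certain.** This stands. A reader might infer that power is necessarily lost, or that any association of the factors with OKS, TUG or strength produces the loss. The article gives no prognostic strength, and stable level differences between strata already drop out of the change contrast. At R² = 0 nothing is lost.

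**Validity is not threatened.** This also stands. A reader might suspect false-positive findings, but the error goes in the conservative direction.

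**Strength units.** A reader might infer that newtons and newton-metres are pooled. They are not: both are expressed as newton-metres per body weight, and a constant additive device offset cancels from change. What remains is that device and site coincide, so a difference in scale or variance between devices would be a site difference that the model does not represent. The article gives no figure for one, and strength is a secondary outcome.

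**Other causes of low power are larger.** Correct: the recruitment shortfall alone takes power from 80.8% to 54.5%.

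**Conclusion.** The mismatch between the stratified allocation and the stated fixed effects is real. Its consequence is a conditional loss of efficiency. For OKS the gain from adjustment is uncertain: none if the factors do not predict change, about 2 to 4 points of power at R² of 0.05 to 0.10, and about 15 points only at 0.30. For the co-primary TUG some gain is likely, about 4 to 9 points under the assumptions above.

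These sizes rest on an assumed R², equal arms of 23, the article's SD of 8 and a 5-point difference. The point is worth acting on because the change is cheap, the trial is small, and the factors were needed to choose each participant's envelope and so are known for everyone randomised.

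**What to change.** In all between-group models, do one of the following:

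- Keep baseline as a response and add site, gender and TUG stratum **with their interactions with time**.
- Model the 2- and 4-month values (and 12 months in the secondary analysis) with the outcome's baseline value and the stratification factors, each by visit, as covariates. For TUG in this form, continuous baseline TUG replaces the TUG stratum; it cannot be both a response and a covariate.

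Main effects alone in the first form are not enough. For the strength outcomes, include site × visit and consider a site-specific residual variance.

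Cost: wording of the analysis plan and no new data. In the primary model with three visits, the first form adds 3 factors × 3 visits = 9 parameters. The second adds 3 × 2 = 6 for the factors and 2 for baseline by visit; for TUG it is 2 × 2 = 4 plus 2. On about 46 participants this is a small but real cost, with little or no return where the factors do not predict change. At R² = 0 the calculated loss is about 0.1 point of power. The choice should be fixed before the arms are compared, or labelled as post hoc.

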**Methods:**

This was a dual-center, nonblinded, two-arm, parallel group randomized controlled trial with an embedded qualitative approach. This study aimed to recruit 100 patients who underwent their first unilateral TKR (aged 60-75 years). Participants were randomized to the exergame or standard home exercise arms. Participants followed a custom-made exergame program independently at their homes daily for 4 months. The primary outcomes at 4 months were function and pain related to the knee using the Oxford Knee Score questionnaire and mobility using the Timed Up and Go test. Other outcomes, in addition to physical function, symptoms, and disability, were game user experience, exercise adherence, physical activity, and satisfaction with the operated knee. Assessments were performed at the preoperative baseline and at 2, 4, and 12 months postoperatively. Exergame adherence was followed from game computers and using a structured diary. Self-reported standard exercise was followed for 4 months of intervention and physical activity was followed for 12 months using a structured diary. Qualitative data on patients’ perspectives on rehabilitation and exergames were collected through laddering interviews at 4 and 12 months.

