## Methods

### Trial Design

This was a 4-month dual-center, two-arm, parallel group randomized controlled trial that determined the effectiveness of exergame-based home-based rehabilitation by comparing it with standard home exercise after TKR. The 4-month intervention period was followed by the 8-month follow-up period. Participants’ perspectives on rehabilitation and exergames were explored using an embedded qualitative approach. Figure 1 illustrates the flow of this study.

Figure 2 presents the enrollment schedule, interventions, outcome assessments, and interviews. The participants’ functioning, disability, and symptoms were assessed preoperatively *at t_0_* (baseline) and postoperatively *at t_1_*, *t_2_*, *and t_3_* (2nd, 4th, and 12th month, respectively). Individually arranged assessments were conducted in the exercise laboratory at the Turku University of Applied Sciences and the exercise laboratory at the University of Jyväskylä. Research data were collected before TKR surgery at baseline and during the RCT intervention and follow-up periods. The baseline assessment (*t_0_*) was performed within 2 weeks before the planned day of surgery. During the baseline assessment visit, participants provided written informed consent, after which the research physiotherapist measured the outcomes, performed randomization, and guided home exercising according to the allocation group. The postoperative assessments (*t_1_,*
*t_2_*, and *t_3_*) were performed within +5 or −5 days of the postoperative 2-, 4-, and 12-month time points. During the postoperative assessment visit, the research physiotherapist measured the outcomes (*t_1,_*
*t_2_*, and *t_3_*) and guided the PA of standard care and the gym work out for strength training (*t_2_)*.

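### The primary mixed model leaves the arms' baseline means free to differ, so its 4-month contrast is in effect a change-score comparison: valid, but less precise than the pre-randomisation baseline allows

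*Protocol article*

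**What the plan says.** All references are to the Protocol article.

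- **Model (Data Analysis Plan).** "Repeated measures of the changes in primary and secondary outcomes will be compared between the exergame and standard home exercise groups", by intention to treat, with mixed effects models and an unstructured covariance. "Fixed effects included group, time, and group × time interactions". No baseline covariate and no common baseline mean is mentioned.
- **Visits in the primary model (same section).** "In the primary analysis, repeated measurements will be taken at different time points, including at baseline and at 2 and 4 months". The 12-month analysis is to use similar models. The section also commits to analysing whatever data each participant contributes, without imputation.
- **Primary time point (Abstract, Methods).** "The primary outcomes at 4 months were function and pain related to the knee using the Oxford Knee Score questionnaire", together with mobility on the Timed Up and Go (TUG) test.
- **Timing of baseline (Trial Design; Random Allocation).** Outcomes are measured at the baseline visit and allocation follows. Randomisation is stratified by site, gender and baseline TUG cut at 10 seconds. The Oxford Knee Score (OKS) is not a stratification factor.
- **Size (Sample Size; Results).** "Assuming a mean difference of 5 (SD 8) points [40] in a change in the OKS between the groups at 6 to 12 months", "a sample size of 42 in the intervention and control groups was required to detect differences between groups at an α of .05", with 80% power. The target was 100. In the event 52 consented, and 46 of them had at least one postoperative measurement.

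**The concern.** When group, time and their interaction are all unrestricted and baseline is one of the times, the model has a separate mean for every arm at every visit, including baseline. The group × time contrast at 4 months is then the arm difference at 4 months minus the arm difference at baseline. Any arm difference at baseline arose by chance, because the measurement came before allocation. Subtracting it in full adds noise unless the 4-month value regresses on baseline with slope 1. Adjusting for baseline, or forcing one baseline mean, subtracts only the part that the correlation supports.

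What is at stake is the width of the confidence interval for the primary effect. The article's Strengths and Limitations section already says the trial is probably underpowered. Recruitment is closed, so the efficiency of the analysis is one of the few things that can still be improved.

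**Working it through.** **1. The plan's own figure.** Difference 5, SD of change 8, two-sided α 0.05 (sidedness is not stated, but a one-sided test would need only 32 per arm), power 80%. The normal approximation gives 41 per arm. The two-sample t-test gives 79.8% power at 41 and 80.8% at 42. The stated 42 per arm reproduces, and the SD of 8 belongs to the change score.

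**2. What the stated model estimates.** Take 23 per arm (46 split evenly, an assumption) with complete data.

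- Difference in mean change: SE = 8 × √(2/23) = 2.359.
- Generalised least squares on the three-visit model with free baseline means: SE of the 4-month interaction contrast = 2.359.

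The two are identical. With 3 extra baseline-only participants per arm (6 in all, the 52 − 46 without any postoperative measurement), the free model gives SE 2.31 to 2.34. The equivalence is then close rather than exact.

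**3. What baseline adjustment gives.** Let s0 and s4 be the SDs at baseline and 4 months, ρ their correlation, and q = s4/s0. Per-participant variances are:

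- change: s0² + s4² − 2ρ·s0·s4
- adjusted: s4²(1 − ρ²)
- gap: (s0 − ρ·s4)², which is never negative
- ratio, adjusted to change: q²(1 − ρ²) / (1 + q² − 2ρq), which is (1 + ρ)/2 when q = 1

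The documents give neither ρ nor q, so both are varied:

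| q | ρ = 0.3 | ρ = 0.5 | ρ = 0.7 |
|---|---|---|---|
| 0.8 | 0.50 | 0.57 | 0.63 |
| 1.0 | 0.65 | 0.75 | 0.85 |
| 1.25 | 0.78 | 0.89 | 0.98 |

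Two cells written out: q = 0.8, ρ = 0.5 gives 0.64 × 0.75 / (1.64 − 0.80) = 0.57. And q = 1.25, ρ = 0.7 gives 1.5625 × 0.51 / (2.5625 − 1.75) = 0.98.

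At q = 1, least squares with one common baseline mean (2-month to 4-month correlation assumed 0.7) gives SEs of 1.90, 2.04 and 2.17, which matches the formula. With the baseline-only participants included, the variance ratios are 0.68, 0.77 and 0.87, so the loss persists.

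**4. Power for 5 OKS points at 23 per arm, SD of change held at 8, t-test.**

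- As planned: 54.5%.
- Adjusted, q = 1: SD = 8 × √ratio, with the variance raised by 1 + 1/42 (about 2%) for the extra estimated coefficient. Power is 72%, 66% and 60% at ρ = 0.3, 0.5 and 0.7.
- Without that allowance, a change analysis would need 46/0.65 = 71, 46/0.75 = 61 or 46/0.85 = 54 participants to match 46 analysed with adjustment.
- At q = 1.25 and ρ = 0.7 the allowance cancels the gain: 0.98 × 1.024 is about 1.00.

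**5. Is 23 per arm right?** It is probably optimistic. The 46 had at least one of the 2-, 4- or 12-month measurements, not necessarily the 4-month one. For TUG the number may be lower, because the list of mailed outcomes (Promotion of Participant Retention) does not include it.

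**The case against.** The best defence is that this is a legitimate, widely used model and that the article is coherent: outcomes are described as changes, the sample size is built on a change, and the analysis compares changes. That stands. The point is about efficiency, and nothing in the section is misstated.

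Several further limits also stand:

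- The gain depends on a correlation and an SD ratio that the documents do not give, and in part of the plausible range it is negligible.
- Stratifying on dichotomised TUG limits chance imbalance in that outcome, though not in OKS.
- Data collection has ended and neither participants nor trial personnel were blinded after assignment, so changing the primary model now is not cost-free.
- A model with only 2- and 4-month responses drops the 6 participants with no postoperative measurement, which sits awkwardly with the commitment to use all data.

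A reader might also infer that the plan cannot be fitted: if "Repeated measures of the changes in primary and secondary outcomes will be compared" meant change scores as the response, the baseline row would be zero for everyone and the three-visit covariance singular. The text does not support this. It speaks of measurements at three visits, and the natural reading is observed values, with change assessed through the interaction.

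None of this removes the core point. The article itself fixes the visits and fixed effects of its primary model, and that model makes poor use of a pre-randomisation baseline.

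**Conclusion.** The concern holds as a loss of precision. The planned 4-month contrast is in effect a difference in mean change, exactly so with complete data. Using the baseline properly is never less precise asymptotically. With equal SDs the variance falls to 0.65–0.85 of the planned value for ρ from 0.3 to 0.7. Across assumed SD ratios of 0.8 to 1.25 the figure moves between about one half and almost no gain. For OKS under equal SDs, power rises from about 55% to about 60–72%, on an optimistic 23 per arm.

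Two stronger conclusions should not be drawn. The planned estimate is not biased: over randomisation both approaches target the same effect, although a chance imbalance does enter one trial's change-score estimate. Nor does adjustment rescue the sample size: under equal SDs it does not bring power back to 80%. No gain was computed for TUG.

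**What to change.** Reword the Data Analysis Plan so that:

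1. The response is the observed value at baseline, 2 and 4 months, with unstructured covariance and **one common baseline mean for both arms** (visit effects plus group effects at the postoperative visits only). This keeps everyone with any measurement.
2. Alternatively, the responses are the 2- and 4-month values, with group, visit, group × visit, baseline and baseline × visit as fixed effects. This version leaves out participants with no postoperative measurement, and the plan should say so.
3. The group difference at 4 months is named as the primary estimate for OKS and for TUG.
4. The 12-month analysis takes the same form.

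No new data are needed, since outcomes were measured before randomisation. The cost is procedural. Because the trial is unblinded and data collection is complete, the change must be dated and justified before any between-group outcome comparison, and the model as published should be reported as a sensitivity analysis. If a comparison has already been made, the published model should stay primary and the adjusted one be labelled as supplementary.
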